**Secondary health outcome**				
Self-reported 7-day point prevalence abstinence at the end of pregnancy among pregnant smokers and recent quitters. (Aim 1)	Structured telephone interview^a^	Postpartum women	Within 2 weeks after giving birth	Self-reported 7-day point prevalence abstinence will be analysed in the same way as the primary outcome.
**Intervention outcomes**				
Documented provision of smoking cessation support (SCS) at booking visit and any subsequent visits. Offer of: • referral to a smoking cessation service including NSW Quitline • behavioural support • nicotine replacement therapy (Aim 2)	Deidentified data extraction of specified variables for all births to eligible women at intervention sites	*e*Maternity^b^	Throughout the 32-month collection period	• *e*Maternity SCS scores will be calculated based on the documented provision of SCS in *e*Maternity for each woman at each visit. • Scores will be modelled using a linear mixed model. Fixed effects will be included for time, intervention, and the interaction of these. •Random effects for site and participant will be included to account for clustering by site, and repeated measures on participants. •The interaction term will directly compare the rate of change in SCS scores over antenatal visits between pre and post-intervention.
Self-reported: • Provision of Advice to quit smoking • Provision of Assistance to quit smoking • Provision of referral to a quit smoking service (e.g. NSW Quitline or local service). (Aim 3)	Study specific questionnaire	Clinicians	Before training and 6 months post-training	• The outcome measure will be a composite score of self-reported provision of SCS, calculated from the questionnaires completed by clinicians prior to training and at 6 months post-training. • Post-intervention clinician SCS scores will be modelled using a linear mixed model. Fixed effects will be included in the model for the pre-intervention SCS score and time. A random effect will be included for site to account for randomisation by cluster.
Women’s reported receipt of: • Advice on quitting • Referral to a quitting program • Written self-help materials (Aim 5)	Structured telephone interview^a^	Postpartum women	Within 2 weeks after giving birth	• Receipt of SCS reported by women will be modelled using logistic regression in a generalised linear mixed model framework. Fixed effects for time and intervention will be included in the model and a random effect for site will be used to account for randomisation by cluster.
**Mediators** (for more detail on the identified barrier, intervention types, behaviour change techniques and measures, see Additional file 1)				
• Capability • Personal priority • Tracking systems • Work environment • Effectiveness of Quitline referral • Client relationship • Lifestyle choice • Personal discomfort (Aim 4)	Study-specific questionnaire	Clinicians	Before training, immediately post-training and 6 months post-training	• Factor analysis of the initial questionnaire used to identify barriers/enablers identified several factors that predicted provision of SCS (e.g. capability, personal priority). These are included in the current questionnaire with clinicians. • Additional items to measure constructs/barriers identified in our qualitative research, but not in the original questionnaire have been added to enable assessment of whether these barriers have been addressed. • Initially, confirmatory factor analysis will be undertaken to confirm the factor structure. • A composite score across all items within each of the factors will be the outcome measure. • Any items not loading onto a factor will be modelled separately. • To assess changes in factor scores the total score on each factor will be modelled using a linear mixed model where one parameter will estimate the score immediately post-intervention and another parameter will estimate the score 6 months after intervention. The model will adjust for pre-intervention total score and time. A random effect will be included for site to account for randomisation by cluster. • Note - work environment will only be assessed immediately pre-training and 6 months post-training, as this is unlikely to have changed during the training.

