### Study design

The study is being undertaken as a partnership between academic researchers, policy makers within NSW State Government and non-government agencies and senior clinicians from participating sites. At each site, there is a Midwifery Partner Investigator and an Obstetric Partner Investigator supporting implementation of the trial.

The MOHMQuit trial is a pragmatic stepped-wedge cluster-randomised controlled trial of an implementation intervention in nine public maternity services in NSW. Our overarching goal is to increase smoking cessation among pregnant women to improve health outcomes. This trial will test the effectiveness and cost-effectiveness of the MOHMQuit intervention in achieving this, while also testing the mechanisms of action of the strategies based on the underpinning theoretical development of MOHMQuit. The specific aims of the trial are to compare the effectiveness of MOHMQuit versus usual care in increasing:Smoking cessation among pregnant women attending public antenatal services in NSW;The provision of guideline-recommended SCS as documented in *e*Maternity;Participating clinicians’ self-reported provision of guideline-recommended SCS to pregnant women;Participating clinicians’ knowledge, skills, confidence and positive attitudes regarding providing guideline-recommended SCS to pregnant women; andWomen’s reported receipt of cessation advice, resources and referral to quit smoking services.

Additional aims include the following:6.Determining the cost-effectiveness of the intervention in increasing smoking cessation;7.Assessing implementation of the intervention through a detailed process evaluation;8.Examining the mechanisms of action of the intervention strategies and moderators of their impact.

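### The Aim 3 clinician model, as written, cannot estimate MOHMQuit versus usual care, and the Aim 4 wording points to the same fault

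*Protocol article*

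**What the plan says.** In the protocol article, Study design, the first five aims share one stem: to "compare the effectiveness of MOHMQuit versus usual care in increasing" a list of outcomes. Aim 3 is clinicians' self-reported provision of guideline support. Aim 4 is their knowledge, skills, confidence and attitudes.

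Table 2, Intervention outcomes, Aim 3: questionnaires are taken "Before training and 6 months post-training". The analysis reads "Post-intervention clinician SCS scores will be modelled using a linear mixed model", then "Fixed effects will be included in the model for the pre-intervention SCS score and time". A random effect for site completes the model.

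Table 2, Mediators, Aim 4: questionnaires are taken "Before training, immediately post-training and 6 months post-training" (work environment is not asked immediately after training). The analysis begins "To assess changes in factor scores the total score on each factor will be modelled" and specifies that "one parameter will estimate the score immediately post-intervention and another parameter will estimate the score 6 months after intervention". It then adds "The model will adjust for pre-intervention total score and time", with a random effect for site.

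In the same table, the models for the primary outcome, Aim 2 and Aim 5 each name a fixed effect for intervention.

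**The concern.** A comparison with usual care needs outcome observations made under usual care, and a parameter that separates them from those made under the intervention. The Aim 3 model has neither. Run as written, it describes how 6-month scores vary with pre-training score and calendar time. It says nothing on whether MOHMQuit raised them.

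The natural fallback is a mean pre/post change. Over six months that change mixes the training effect with any secular drift. The article itself reports COVID-19 impacts and redesign of the electronic record around this period, so drift is plausible. Two of the five effectiveness aims could be reported as a randomised comparison when the estimate is an uncontrolled one.

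**Working it through.** The article gives no sample size or effect size for Aims 3 and 4, so there is no planned figure to reproduce. The check is whether the effect is identifiable, followed by the precision of the remedy.

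**1. Aim 3 as written.** Each clinician contributes one outcome row, at 6 months after training. Columns: intercept, pre-score, time. Rank 3 of 3. An added intervention column equals 1 in every row, which is the intercept: 4 columns, rank 3. Reading time as survey occasion does not help, because occasion is constant across these rows.

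**2. Aim 4, with the pre-score as covariate.** Columns: immediate indicator, 6-month indicator, pre-score, time. Rank 4 of 4. An intervention column is the sum of the two indicators: 5 columns, rank 4. If pre-training scores were instead outcome rows and the reference level, the two indicators would be the contrasts wanted.

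**3. What a pre/post change would show.** It equals effect plus six-month drift. Effects of 0.50, 0.25 and 0 with drifts of 0, 0.25 and 0.50 all sum to 0.50.

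**4. Stacking pre and 6-month scores.** Assume nine one-site steps two months apart. Intercept, intervention and linear time give rank 3 of 3; with categorical time, 13 of 13. In a small simulation (100 runs per scenario, some convergence warnings) this model averaged 0.51, 0.27 and 0.03 for true effects of 0.50, 0.25 and 0.

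**5. Where that information comes from.** Put site in as fixed effects. With linear time the rank is 10 with or without the intervention column; with categorical time it is 18 with or without. The reason is general: each within-site difference is θ + f(t+6) − f(t), and the trend f(t) = t/6 reproduces a unit effect at every site whatever the step dates. So the 6-month effect is identified only between sites, through the random-site assumption. Aim 4's immediate indicator is not absorbed: with linear time it raises the rank from 10 to 11.

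**6. Precision (assumptions, not from the documents).** Take m = 30 clinicians per site, clinician SD 0.7, residual SD 0.7, site SD σ_s, site-by-time SD σ_st and common linear drift. Site mean survey times are 2 months apart, so Sxx = 4 × 60 = 240.

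- Within-site part: W = 2(0.49/30 + σ_st²)/9
- Between-site part: B = σ_s² + 0.49/30 + (0.49/30 + σ_st²)/2
- Var(θ) = W + 36B/240

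| σ_s | σ_st | W | B | SE(θ) | SE, simple pre/post = √W |
|---|---|---|---|---|---|
| 0.1 | 0 | 0.0036 | 0.0345 | 0.09 | 0.06 |
| 0.3 | 0 | 0.0036 | 0.1145 | 0.14 | 0.06 |
| 0.3 | 0.2 | 0.0125 | 0.1345 | 0.18 | 0.11 |

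With categorical time, the same calculation by generalised least squares gives 0.10, 0.15 and 0.19.

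**7. Clinician correlation in Aim 4.** Two post-training scores per clinician enter a model whose only stated random effect is site. If their residual correlation is ρ, omitting it overstates the SE of the immediate-to-6-month change by 1/√(1−ρ) and understates that of the post-training mean by √(1+ρ). For assumed ρ of 0.3, 0.5 and 0.7 these are 1.20, 1.41, 1.83 and 1.14, 1.22, 1.30.

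**The case against.** **Aim 4 may already be sound.** Its text is introduced as assessing change and names two post-training parameters, which could be contrasts against pre-training. This stands as an ambiguity. The sentence on adjusting for the pre-training score points the other way, so the wording needs settling, but it does not prove the effect inestimable.

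**Drift does not threaten everything.** The pre-training and immediate surveys bracket a one-day workshop, or about two hours for obstetricians. Calendar time hardly moves, so that change is nearly free of drift. This stands; the drift concern applies to the 6-month scores.

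**The detail may sit in a fuller analysis plan.** This holds partly for clinician-level correlation, which a condensed article may leave out; that sub-point is minor. It does not hold for Aim 3, where the article states outcome, fixed effects and random effect, and the result is wrong rather than incomplete.

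**Other outcomes carry the effectiveness claim.** The primary outcome and Aims 2 and 5 have explicit intervention terms. This stands and limits the severity.

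A reader might also infer that the staggered training dates separate effect from trend cleanly once the model is corrected. They do so only between nine sites, at a clear cost in precision. Nor can the number of survey dates with both trained and untrained sites be stated: a site was added, the final site was brought forward, and the schedule figure is not shown.

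**Conclusion.** For Aim 3 the point is firm: the stated model has no usual-care outcomes and no intervention parameter, so it cannot deliver the comparison in Study design at any sample size. This follows from the article's wording and needs no numerical assumption. For Aim 4 it is conditional on the pre-training score being a covariate, which the wording suggests but does not settle.

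It would be too strong to say that the trial's data cannot answer Aims 3 and 4, or that both models are certainly inestimable. The pre-training questionnaires are collected, and only their place in the model is at fault. The standard errors of about 0.09 to 0.19 against about 0.06 are illustrative: they rest on assumed variances, 30 clinicians per site and equal two-month steps, and the comparator itself rises to 0.11 with site-by-time SD 0.2. Severity is should-fix: the primary outcome and its sample size are untouched.

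**What to change.** Respecify both models in Table 2 and the analysis plan:

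- Use pre-training and post-training scores as outcomes, and do not also enter the pre-training score as a covariate.
- Aim 3: fixed effects for intervention status and calendar time of survey. Aim 4: separate immediate and 6-month indicators against pre-training, plus calendar time (no immediate indicator for work environment).
- Random effects for site and clinician, and for site-by-time if estimable.
- State that the 6-month effect is separated from secular trend only by comparison between nine randomly ordered sites, and is less precise for that reason, while the pre-to-immediate change is nearly free of drift.

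If this model is not adopted, reword Aims 3 and 4 as uncontrolled pre/post changes. Either route changes wording only and needs no new data. The first route costs precision; the second gives up the claim of a comparison with usual care.

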#### Clinical midwifery educator training

Clinical midwifery educators will be provided training and resources to continue to deliver training following the intervention phase, to address issues of staff turnover or absence, in order to maximise sustainability of the intervention. Clinical midwifery educators will attend the 1-day training with the midwives and Aboriginal health workers, and then an additional 1 h training on how to provide the training themselves.

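### The clinician mediator model (Aim 4) fits two post-training scores per clinician but states a random effect for site only, so a comparison of the 6-month with the immediate score would carry too large a standard error

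*Protocol article*

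**What the plan says.** In Table 2 of the protocol article, the mediators row (Aim 4) lists the clinician questionnaire timepoints as "Before training, immediately post-training and 6 months post-training". The factor scores go into one linear mixed model in which "one parameter will estimate the score immediately post-intervention and another parameter will estimate the score 6 months after intervention". The row continues: "The model will adjust for pre-intervention total score and time. A random effect will be included for site to account for randomisation by cluster". No other random effect and no residual covariance is mentioned. Work environment is the exception among the mediators: it is measured once before training and once at 6 months.

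Two other rows of the table help in reading this one.

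- **Aim 2** (documented support in eMaternity) has several scores per woman, and the plan says "Random effects for site and participant will be included to account for clustering by site, and repeated measures on participants".
- **Aim 3** (clinicians' self-reported support) has timepoints "Before training and 6 months post-training", so one post-training score per clinician, and a site effect only.

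**The concern.** Adjusting for the pre-intervention score requires questionnaires linked by clinician, so the two post-training scores in the Aim 4 model come largely from the same people. A site-only random effect is coherent for Aim 3, which has one outcome per clinician. Aim 4 uses the same structure with two outcomes per clinician. It leaves out the person-level term that the table includes for Aim 2 expressly because measures are repeated.

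What is at stake is the comparison between the two time points, that is, whether a gain in capability, personal priority and the other factors seen just after training is still present at 6 months. If the two scores are treated as independent given site and pre-score, the uncertainty of that comparison is overstated and a real fall can be missed. There is a second, conditional issue. Without a within-clinician link, the model cannot use the immediate score of a clinician who is lost by 6 months to inform the 6-month estimate.

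**Working it through.** **Inputs.** From Table 2: two post-training scores per clinician, adjustment for pre-score and time, random effect for site only. From the site eligibility section: nine sites. The article gives no clinician numbers, SD, correlation, dropout rate or power for Aim 4, so there is no figure of its own to reproduce. Assumed: two-sided 5% level (the article states 5% for the primary analysis), and residual correlation r of 0.3 to 0.7 between a clinician's two scores after site and pre-score.

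**Step 1: standard error with complete data.** Let n clinicians each have two scores with residual variance σ².

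- True SE of (6-month − immediate): √(2σ²(1−r)/n)
- SE reported by a model with independent residuals: √(2σ²/n)
- Ratio: 1/√(1−r)

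**Step 2: size and power of that comparison.** The stated model rejects when the absolute difference exceeds 1.96·√(2σ²/n). In units of the true SE the critical value is 1.96/√(1−r).

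- True size = 2[1 − Φ(1.96/√(1−r))]
- For a fall that a correct model detects with 80% power, δ = (1.96 + 0.84) true SEs = 2.80 true SEs, so power = 1 − Φ(1.96/√(1−r) − 2.80). The number of clinicians cancels.

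| r | SE ratio | critical value in true SEs | true size of nominal 5% test | power where a correct model has 80% |
|---|---|---|---|---|
| 0.3 | 1.20 | 2.34 | 1.9% | 68% |
| 0.5 | 1.41 | 2.77 | 0.6% | 51% |
| 0.7 | 1.83 | 3.58 | 0.03% | 22% |

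A simulation agrees at r = 0.5. It used 3,000 runs per setting, nine sites with an assumed 30 clinicians each, site variance 0.02 and residual SD 1. Site was fitted as fixed in both models, and r was treated as known in the corrected one. With a true fall of 0.17 SD, the site-only model rejected in 52% of runs and the model with within-clinician correlation in 81%. Under no change, the corrected model's average SE was 0.061 against an empirical 0.060, with size 5.0%; the site-only model reported 0.086.

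**Step 3: loss by 6 months.** Same simulation, no true change, 30% of clinicians assumed lost. The figures are the bias in the 6-month minus immediate estimate, in residual SD, under the site-only model.

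| how loss depends on the immediate score (given pre-score and site) | r = 0.3 | r = 0.5 | r = 0.7 |
|---|---|---|---|
| not at all | 0.00 | 0.00 | 0.00 |
| lower scorers lost more, log-odds slope 0.5 per SD | +0.04 | +0.07 | +0.10 |
| lower scorers lost more, log-odds slope 1 per SD | +0.07 | +0.12 | +0.17 |

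At slope 1 the site-only model rejects in 9%, 18% and 43% of runs at r = 0.3, 0.5 and 0.7, although nothing changed. With within-clinician correlation the bias is at most 0.004 SD and rejection is 4.4% to 5.6% in all the score-dependent settings at 30% loss. The bias therefore appears only in the rows where loss depends on the immediate score.

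**The case against.** The strongest reply is that the plan never states a test of decline. Aim 4 is to increase knowledge, skills, confidence and attitudes, and the row gives one estimate per time point, adjusted for the pre-score. With complete data each estimate's own standard error is roughly right. This stands: a reader might infer that the plan tests a fall with a wrong standard error, but no such test is named. What remains is that two separate parameters in a model meant to assess change invite the comparison, and the article counts sustainability among its interests (Discussion, advantages of the stepped-wedge design).

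A reader might also infer that the 6-month result is biased by dropout. The article does not support that. It gives no rate or pattern of questionnaire loss. Its phrase "to address issues of staff turnover or absence" explains why educators are trained to go on delivering training; it does not forecast survey non-response. Loss completely at random, or loss explained by pre-score and site, causes no bias.

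Nor does the model treat the two scores as coming from wholly unrelated people. The shared pre-score and site effect absorb part of the correlation, and only the remainder is ignored. For the contrast with complete data the error is conservative: it can hide a fall but not create one.

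Finally, a condensed article may leave residual covariance to an analysis plan that is not shown. This is fair in part. But the row does state its random effect and the reason for it, and the same table names a participant effect where repeated measures were recognised. Read as written, the two rows are inconsistent.

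**Conclusion.** The point holds in limited form. The Aim 4 row specifies two outcomes per clinician with a site effect only, so the within-clinician correlation left after site and pre-score is fixed at zero, contrary to the table's own handling of repeated measures in Aim 2. A comparison of the 6-month with the immediate score taken from this model would have a standard error too large by 20% to 83% for r between 0.3 and 0.7. The cost in power is 12 points at r = 0.3, 29 at r = 0.5 and 58 at r = 0.7, measured from 80%. These sizes rest on assumed correlations and on a contrast that is natural but not named. Bias from dropout is a possible risk, not an established fault.

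The reach is narrow. Work environment has a single post-training score and is unaffected. So are the primary outcome and the Aim 8 mechanism analysis, which uses pre-training and 6-month data only. The correction is worth making because it is cheap and removes an inconsistency, but the trial's main result does not depend on it.

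**What to change.** In the Aim 4 row of Table 2, or in the analysis plan, make these changes:

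- State random effects for site and for clinician within site, to account for clustering and for repeated scores on clinicians. An unstructured residual covariance over the two post-training scores would also serve.
- Include every clinician with at least one post-training score, and state the missing-data assumption: loss may depend on pre-score, site and the immediate score, but not otherwise on the unseen 6-month score.
- Take any 6-month minus immediate contrast from that model.
- Leave the work environment analysis as it is.

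The cost is a sentence or two of text and one extra variance parameter (slightly more with an unstructured covariance). No new data are needed, because adjusting for the pre-score already requires linked questionnaires.

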**Moderators**				
Leadership (Aim 8)	Study specific questionnaire includes the *Implementation Leadership Scale* [57]	All leaders involved in training	Three months after leader training	• The Implementation Leadership Scale (supervisor version) is comprised of twelve items that make four subscales: the proactive subscale, the knowledgeable subscale, the supportive subscale, and the perseverant subscale. • For each subscale, a mean score for each set of items that load onto the relevant subscale will be computed. Additionally, a mean of the scale scores will be computed to generate the total score for the Implementation Leadership Scale [57]. Scores will be computed for each clinician and an aggregated clinical level score will be calculated.
	Study specific questionnaire includes the *Leadership Engagement Scale* [58]	Clinicians	6 months post-training	The Leadership Engagement Scale is comprised of four items. A mean score for these items will be computed for each clinician. An aggregated clinic level score will also be calculated.
	Interviews	Selected leaders	6 months post-training	Analysis of qualitative data is described below under process evaluation.
Implementation climate (Aim 8)	Study-specific questionnaire includes the *Implementation Climate Scale* [58]	Clinicians	6 months post-training	The Implementation Climate Scale is comprised of four items. A mean score for these items will be computed for each clinician. An aggregated clinic level score will also be calculated.
